**Methods:**

This study is a short-term multicenter randomized control trial with a crossover design. Patients consecutively admitted to 4 inpatient treatment centers were invited to participate in 3 conditions, each lasting 45 minutes, within one week. The order of the conditions was randomized. There were a total of 5 assessments, taken at baseline, immediately before each condition, immediately after each condition, and 1, 2, and 4 hours postintervention, enabling patterns of change over time to be observed. Psychological effects were assessed with self-report questionnaires, which included scales for craving, state anxiety, positive and negative affect, self-esteem, and mood. Exercise intensity was assessed with the Borg Rating of Perceived Exertion scale and a heart rate monitor (Polar M200; Polar Electro Ltd). Cortisol was assessed in saliva before and 4 hours after the intervention.

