### Study Design and Randomization

This study is a short-term, multicenter randomized controlled trial with a single pretest and multiple posttests. Using a crossover design, changes in mood, craving, state anxiety, affect, and self-esteem were assessed by comparing the initial measurement (taken immediately before exercise) with 4 follow-up assessments, first immediately after exercise, then at 1, 2, and 4 hours postintervention. The design allows the pattern of change over time to be seen.

Participants completed 3 sessions—2 supervised group exercise sessions (soccer and circuit training) and 1 control condition (attending a lecture about the health benefits of physical activity)—within the same week. All the sessions were performed in a group setting.

The order of the study conditions was determined by a random number generator and placed in sealed envelopes at a site separate from the study location. When a group of suitable patients (5-10 patients) was recruited at a site, a sealed envelope with the order of exercise and control conditions was drawn by a person outside of the research group.

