### Procedure

Patients were invited to attend an information meeting, where members of the research group explained the purpose of the study in detail and handed out written information. To minimize dropout, the recruitment took place a maximum of two weeks ahead of the trial. A member of the research group visited the treatment center 1 week before the study to answer questions.

After giving informed consent, eligible participants were gathered to perform the interventions and assessments. These sessions were undertaken on-site at the clinics starting at 9:30 AM on Monday, Wednesday, and Friday within one week. The participants were asked to refrain from doing exercise on the days of the trial and on the days in between the interventions to give a 1-day washout period between the sessions. All sessions lasted 45 minutes. During the week of the trial, all participants received treatment as usual between the sessions.

The following exercise activities and control condition were tested in random order: (1) indoor soccer, (2) circuit training in a gymnasium using body weight, and (3) the control condition, attending a lecture on exercise and mental health.

Across all trial days, the participants were advised to eat breakfast about an hour before starting the trial. They were advised to have a light meal or snack after training, have lunch on all trial days, and keep hydrated throughout the day. Participants were also asked to limit the use of caffeine and nicotine during the test period. The flow of participants through the trial is shown in Figure 1.

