### Statistical Analyses and Power Calculation

Statistical power was estimated using G*Power (version 3.1.9.7; Heinrich-Heine-Universität Düsseldorf). Parameters were based on results from our feasibility study [36] and also took into account previous studies demonstrating medium effect sizes for acute exercise on mood states [38,45]. Assuming an effect size of 0.3 and power (β) of .8, with 3 groups and 5 measurement points, we estimate needing at least 21 participants to test our hypotheses. We planned to include one group of 5 to 10 participants from each site, which would give us 20 to 40 participants. Due to the experimental study design and the inclusion of only inpatients, we anticipate minimal missing data. Descriptive data will be calculated for each measure. Changes over time will be assessed using mixed (group × time) repeated-measures analysis of variance with post hoc contrasts. If participants return questionnaires with missing data, the missing items will be imputed using the last observation carried forward method. If questionnaires are returned with more than 50% of data missing, the questionnaire will be excluded from the analysis.

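### The named analysis and the sample size treat condition as a between-patient factor, although every patient completes all three conditions

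*Protocol article*

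**What the plan says.** The Abstract (Methods) calls the study a "short-term multicenter randomized control trial with a crossover design". Study Design and Randomization repeats this ("Using a crossover design, changes in mood, craving, state anxiety, affect, and self-esteem were assessed") and has each participant complete two exercise sessions and "1 control condition (attending a lecture about the health benefits of physical activity"). Under Procedure, the three sessions fall on Monday, Wednesday and Friday of one week, and "The following exercise activities and control condition were tested in random order".

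Statistical Analyses and Power Calculation names one inferential method: "Changes over time will be assessed using mixed (group × time) repeated-measures analysis of variance with post hoc contrasts". The sample size in the same paragraph rests on a three-group layout: "Assuming an effect size of 0.3 and power (β) of .8, with 3 groups and 5 measurement points", which leads to a minimum of 21 participants. The Results section reports 39 patients, with analysis still to come.

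**The concern.** A mixed group × time ANOVA crosses a between-subject factor with a within-subject factor. Time is plainly the within-subject factor, which leaves group as the between-subject one. This trial has no between-subject treatment groups: the three conditions are three sessions of the same person. Taken literally, the model would treat 39 patients as 39 × 3 = 117 unrelated subjects.

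Pairing across the five assessments within a session would be kept. Pairing across the three sessions would be lost, and that pairing is the reason for using a crossover. The comparisons at stake are exercise against lecture and soccer against circuit training, on mood (the primary outcome) and on the secondary outcomes. In a trial of 39 people, an effect could be missed because of the model and not because it is absent.

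**Working it through.** **1. The plan's own figure.** Inputs from the article: effect size 0.3 (read as Cohen's f), power 0.80, k = 3 groups, m = 5 measurements. Not given, so assumed: α = 0.05, correlation among repeated measures ρ = 0.5, sphericity. For the within-between interaction:

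λ = N·m·f²/(1 − ρ), df1 = (k − 1)(m − 1) = 8, df2 = (N − k)(m − 1).

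- N = 18: λ = 18 × 5 × 0.09/0.5 = 16.2, df2 = 60, power 0.776
- N = 19: λ = 17.1, df2 = 64, power 0.806
- N = 21: λ = 18.9, df2 = 72, power 0.856

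The minimum is 19, which becomes 21 with three equal groups of 7. The stated 21 is therefore consistent with three separate groups.

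**2. The match is not unique.** A time effect in a single group at f = 0.25, ρ = 0.5 also needs 21 (power 0.793 at N = 20, 0.816 at N = 21). So does a time effect at f = 0.3, ρ = 0.3 with three equal groups. The number alone does not show which design was entered.

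**3. Standard error of a condition contrast.** Let changes from the pre-session assessment have SD 1, with correlation r between a patient's changes in two sessions. With n = 39:

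- unpaired SE = √(2/39) = 0.226, whatever r is
- true (paired) SE = √(2(1 − r)/39)
- ratio unpaired/paired = 1/√(1 − r)

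**4. Power for one pairwise contrast.** Assumed difference 0.5 SD, two-sided 5%. Paired power is from the noncentral t with 38 df. Unpaired power and size are from simulation of the ordinary two-sample t test (76 df) on correlated data.

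| r (assumed) | SE ratio | Power, unpaired | Power, paired | True size, unpaired |
|---|---|---|---|---|
| 0 | 1.00 | 59% | 58% | 5.0% |
| 0.1 | 1.05 | 59% | 62% | 3.9% |
| 0.3 | 1.20 | 60% | 73% | 1.9% |
| 0.5 | 1.41 | 62% | 86% | 0.7% |

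**5. The full interaction test.** Simulation of 39 patients × 3 conditions × 5 times, 2,000 runs per setting. Assumed variances: 0.3 between patients, 0.2 patient-by-session and 0.5 for the rest, of which a share r is patient-by-time. The assumed effect of both exercise conditions is 0.4, 0.3, 0.2 and 0.1 at the four post-session times. The between-subject test has df 8 and (117 − 3) × 4 = 456. The within-person test has df 8 and 38 × 2 × 4 = 304.

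| r | True null rejected, between | Power, between | Power, within |
|---|---|---|---|
| 0 | 4.8% | 29% | 29% |
| 0.1 | 2.5% | 25% | 34% |
| 0.25 | 1.2% | 18% | 41% |
| 0.5 | 0.0% | 7% | 60% |

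The within-person test rejects a true null in 4.3% to 5.1% of runs throughout. The direction agrees with step 4.

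**The case against.** The strongest reply is that group is only loose wording. The article speaks of a control group and of intervention groups in the Objective, Introduction and Conclusions while describing a crossover, so group × time may simply mean condition × time. That stands as a possibility, and it rules out saying that the sessions certainly will be analysed as 117 different people. It does not remove the mismatch: the word mixed, the group × time form and the three-group sample size all point the same way, and nothing in the text makes condition a within-person factor.

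A reader might infer that the figure 21 proves a parallel-group calculation. It does not, since other settings also give 21. A reader might infer that the trial risks a false claim of benefit. Ignoring a positive r works the other way: it makes the tests conservative. A reader might also infer that patients with any missing assessment will be dropped. The article states no such rule; it describes item imputation, a 50% exclusion rule for questionnaires and an expectation of little missing data.

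It is fair, too, that a condensed article may leave period terms and the random-effects structure to a fuller document. Their absence is not the point here; the point is that the model which is stated does not fit the design.

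Finally, the order of conditions is drawn once per recruited group ("a sealed envelope with the order of exercise and control conditions was drawn by a person outside of the research group") and sessions are held in groups. Effects shared within a group could push the standard error the other way. The figures above isolate the loss of within-person pairing and are not a net figure for the trial.

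**Conclusion.** The point holds as a contradiction between the stated design and the stated analysis. The article does not call this ANOVA primary, but it is the only inferential analysis named, so the contradiction reaches every condition comparison.

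The size depends on r, which the article does not give. Over r = 0 to 0.5 the cost runs from nothing to a standard error 1.41 times too large; for an assumed 0.5 SD difference with 39 patients the power given up reaches 86% − 62% = 24 percentage points at r = 0.5. The documents do not support calling the standard errors wrong without qualification: the error is conservative for positive r, it vanishes at r = 0, and it arises only if the sentence is applied literally. Using the within-person model costs about 1 point of power at r = 0, so there is little reason not to specify it.

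**What to change.** Replace the ANOVA sentence with a model in which condition (soccer, circuit training, lecture) is a within-person factor. One suitable form is a linear mixed model with condition × time and day (period) as fixed effects, participant and participant-by-session as random effects, and all available assessments used. Add a participant-by-time term as well, or an equivalent covariance structure: the two random intercepts cancel from a change score, so without this term the model would not pick up the correlation r on which the gain in precision depends.

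Restate the sample-size basis for the same design, giving the effect measure, α and the assumed correlation. As an illustration, for a 0.5 SD pairwise difference at 80% power and two-sided 5%, the normal approximation 2(1 − r) × ((1.96 + 0.84)/0.5)² gives 63, 48 and 32 patients at r = 0, 0.25 and 0.5. With recruitment closed at 39, this serves to state what the trial can detect, not to change enrolment.

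The cost is one paragraph of text and standard software. The article places the analysis after data collection, and no new data are needed.

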The misuse of a single substance is exceptional in SUDs [35]. Whether acute exercise can benefit people with polysubstance dependencies is unclear. Most studies have assessed aerobic forms of exercise, often in laboratory conditions using stationary bicycles [12,28]; little is known about other forms of exercise in clinical settings. With some exceptions [25], psychological benefits across different forms of exercise have not been compared, and it is unclear how long the changes last following a single exercise session. Studies have mostly used pre- and postassessments only, which is a limitation.

To address these questions, we conducted a feasibility study to compare the short-term effects of 3 different exercises (soccer, circuit training, and walking) conducted in nonlaboratory settings [36]. Findings suggested that moderately intense exercise activities performed in natural settings may increase mood, help attenuate drug cravings, increase positive affect, decrease negative affect, and improve self-esteem. The results were promising but need to be replicated with a larger sample and a randomized design.

In this study, we are conducting a multicenter randomized controlled trial to compare the short-term effects of 2 forms of exercise (soccer and circuit training) with a control condition (a lecture on the health benefits of physical activity) in polydrug-dependent inpatients. We chose to compare the effects of exercise to a nonexercising control group (lecture) instead of a walking-based intervention, as previous studies have shown that even light physical activity can have mood-enhancing effects [37]. We are also performing biomarker analyses of cortisol to better understand the underlying mechanisms.

Key research questions that will be addressed include (1) What are the short-term effects of soccer and circuit training on mood (primary outcome), drug craving, positive and negative affect, state anxiety, and self-esteem in adults with SUD? (2) How long do the effects last after the exercise sessions end? (3) Are there differences between the two forms of exercise? (4) Do the effects differ with the intensity of the exercise? and (5) Are the study outcomes associated with changes in the stress hormone cortisol?

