#### Baseline and Follow-up Assessments

Mood (primary outcome), craving, affect, self-esteem, and state anxiety were measured with self-report questionnaires. The same questionnaires were repeated for baseline and follow-up assessments. The questionnaires chosen could be completed in 5 minutes, were amenable to repeated administration, and had sound psychometric properties.

The self-report questionnaires and saliva samples collected immediately before the sessions were the baseline assessment. Following the sessions, participants filled in self-report questionnaires on 4 occasions: immediately after the session and 1, 2, and 4 hours after the session. Immediately after the exercise sessions, participants were also asked to rate the perceived intensity. A saliva sample was gathered 4 hours after all sessions. Figure 2 illustrates the SPIRIT figure, study measures, and assessment time points.

Self-report measures were (1) the Feeling Scale, (2) drug craving, (3) the Positive and Negative Affect Schedule (PANAS), (4) the Rosenberg Self-Esteem Scale, (5) state anxiety, and (6) the Borg Rating of Perceived Exertion (RPE) scale.

First, changes in mood related to exercise were assessed with the Feeling Scale [39] (primary outcome), a single-item Likert scale ranging from –5 (very bad) to 5 (very good). Participants were instructed to indicate how they felt “at this moment.” The scale has been used extensively in acute exercise studies [40].

Second, drug craving was assessed using a single-item visual analog scale (VAS) ranging from 0 (no craving for drugs) to 10 (strong craving for drugs). Participants were instructed to indicate how strong their craving for drugs felt “at this moment.” The instrument has been used in previous studies of acute exercise [41] and it was tested in our recent pilot study [36], where it was shown to be sensitive to change.

Third, the PANAS assesses 2 dimensions of affect [42]. Participants self-rate 20 items on a 5-point Likert scale ranging from 1 (very slightly/not at all) to 5 (extremely). Ten of the items represent positive affect and the others represent negative affect.

Fourth, self-esteem was measured using the 10-item Rosenberg Self-Esteem Scale [43], which measures global feelings about oneself (that is, both positive and negative feelings). All items are answered using a 4-point Likert scale ranging from strongly agree to strongly disagree.

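### Carrying missing items forward across time points dampens the immediate effect and prolongs a fading one, and the undefined 50% rule leaves open whether this reaches the primary outcome

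*Protocol article*

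**What the plan says.** All rules on missing data are in the Protocol article, Statistical Analyses and Power Calculation.

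- Trigger: "If participants return questionnaires with missing data". The rule concerns forms that were handed in with gaps.
- Method: "the missing items will be imputed using the last observation carried forward method".
- Limit: "If questionnaires are returned with more than 50% of data missing, the questionnaire will be excluded from the analysis".
- Expectation: "we anticipate minimal missing data", explained by the experimental design and the restriction to inpatients. No rate is given.
- Analysis: a group-by-time repeated-measures analysis of variance with post hoc contrasts.

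Under Baseline and Follow-up Assessments, the primary outcome is the Feeling Scale, "a single-item Likert scale ranging from" –5 to 5. It is completed before each session and at 0, 1, 2 and 4 hours after it. Craving and state anxiety are also single items. PANAS has 20 items, ten for each dimension of affect, and the self-esteem scale has 10. The second key research question in the Introduction is: "How long do the effects last after the exercise sessions end".

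**The concern.** The Feeling Scale and the craving scale ask how the participant feels at the moment of rating, and the assessments are spaced to show how that state moves. Last observation carried forward fills a gap by assuming that nothing has moved since the previous assessment.

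The consequence depends on where the gap falls:

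- A gap immediately after the session is filled with the pre-session value. That person shows no effect, so the answer to the first research question (the short-term effects) is pulled toward zero.
- A gap at 1, 2 or 4 hours is filled with an earlier value. If the effect is fading, the earlier value is larger, and the answer to the second question (duration) is pulled toward persistence.

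The two questions are therefore biased in opposite directions. In addition, the 50% rule does not tell an analyst what to do with a blank Feeling Scale, because *questionnaire* could mean the whole form or each instrument on it.

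**Working it through.** The plan attaches no figure to this rule, so there is none to reproduce. The section's minimum of 21 participants does not depend on it.

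**Step 1. What the 50% rule does under each meaning of *questionnaire*.** Item counts come from Baseline and Follow-up Assessments: Feeling Scale 1, craving 1, PANAS 20, self-esteem 10, anxiety 1. The sum is 1 + 1 + 20 + 10 + 1 = 33. The Borg rating is left out because it is collected only after exercise sessions; adding it gives 34 and changes nothing of substance (1/34 = 2.9%).

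| | Whole battery | Each instrument |
|---|---|---|
| Textual support | Abstract, Methods: "self-report questionnaires, which included scales for craving, state anxiety, positive and negative affect, self-esteem, and mood" | Baseline and Follow-up Assessments lists and numbers the instruments separately |
| Blank Feeling Scale, craving or anxiety | 1/33 = 3.0%: carried forward | 1/1 = 100%: excluded |
| Most items that can be carried forward | 16 of 33 (48.5%; 17 of 33 is 51.5%) | PANAS 10 of 20, self-esteem 5 of 10 (exactly 50% is not more than 50%) |

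Under the battery meaning, all ten self-esteem items plus mood, craving and anxiety could be blank (13/33 = 39%) and every one would be carried forward. Under the instrument meaning, the ten PANAS items that may be carried could be one entire dimension of affect.

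**Step 2. Size and direction where the rule applies.** Let *d(t)* be the true difference, exercise minus lecture, in change from pre-session, and *q* the chance that the item is blank at each post-session assessment. Assume that the pre-session value is present, and that blanks are independent of the score, of each other and of condition. The expected difference after carrying forward is

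E(t) = (1 − q) · d(t) + q · E(previous assessment), with E(pre-session) = 0.

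The profile is an assumption: d = 1.5, 1.0, 0.5, 0 points at 0, 1, 2 and 4 hours. At q = 5%:

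- 0 h: 0.95 × 1.5 = 1.425
- 1 h: 0.95 × 1.0 + 0.05 × 1.425 = 1.021
- 2 h: 0.95 × 0.5 + 0.05 × 1.021 = 0.526
- 4 h: 0.95 × 0 + 0.05 × 0.526 = 0.026

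| Assumed q | 0 h | 1 h | 2 h | 4 h |
|---|---|---|---|---|
| True | 1.500 | 1.000 | 0.500 | 0.000 |
| 2% | 1.470 | 1.009 | 0.510 | 0.010 |
| 5% | 1.425 | 1.021 | 0.526 | 0.026 |
| 10% | 1.350 | 1.035 | 0.554 | 0.055 |
| 20% | 1.200 | 1.040 | 0.608 | 0.122 |

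The immediate effect shrinks by exactly the fraction q. At 2 hours the overstatement is 0.026/0.5 = 5% at q = 5%, 0.054/0.5 = 11% at q = 10% and 0.108/0.5 = 22% at q = 20%. A different assumed profile (2.0, 1.2, 0.6, 0) behaves the same way: 1.90, 1.24, 0.63, 0.03 at 5% and 1.60, 1.28, 0.74, 0.15 at 20%. Under the same assumptions, an analysis of observed values alone recovers the true profile.

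**Step 3. Multi-item scales.** A scale score is a sum of items, so the recursion holds for it with q as the per-item rate. For one person with 5 of 10 self-esteem items carried forward, and change spread evenly over items, only 5/10 = half of the change since the previous assessment is recorded.

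**The case against.** The strongest reply is that the rule will hardly be used. The plan expects minimal missing data, the questionnaires take five minutes, and the Adherence section puts a member of the research group on site to give reminders and answer questions. At 2% to 5% missing, the largest shift in the main illustration is 1.5 − 1.425 = 0.075 points on a –5 to 5 scale. This stands as to size. It does not change the direction of the bias or settle what the rule means.

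Four stronger readings are tempting, and the document does not support them.

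- *The primary outcome is certain to be carried forward.* This follows only if *questionnaire* means the battery. On the per-instrument meaning, a blank Feeling Scale is excluded and carrying forward never reaches mood, craving or anxiety.
- *The rule covers missed assessments.* It is stated only for returned forms with gaps. A rate of 10% or 20% would require that many participants to hand in a form with this particular item blank, and nothing in the document suggests it.
- *A blank pre-session item takes the 4-hour score of a session two days earlier.* The plan does not say so, and it treats each pre-session assessment as the baseline for its session. It leaves open what is carried into a pre-session gap.
- *Standard errors will be materially too small.* Treating filled values as observed does ignore uncertainty, but the plan gives no missingness rate from which to judge the amount.

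It is also fair to say that dropping the rule while keeping the analysis of variance would not be enough. As usually run, that analysis needs complete data, so a missing score could remove a participant's other time points. The remedy therefore has to include the model.

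**Conclusion.** The concern holds in limited form. The plan prescribes a method that assumes no change between assessments, in a trial designed to measure change between them. Where it applies, it shrinks the immediate effect and, if the effect peaks just after the session and then fades, makes it appear to last longer. If the effect built up after the session, the rule would instead delay its appearance.

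Whether it touches the primary outcome cannot be decided from the text: yes on the battery meaning, no on the per-instrument meaning. On either meaning it applies to PANAS and self-esteem items.

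The bias is probably small if missing data are as rare as the plan expects. It would be noticeable only at rates such as 20%, where 1.5 becomes 1.20 at 0 hours and 0 becomes 0.12 at 4 hours. The profile, the rates, and blanks unrelated to score and condition are assumptions. The point is that the rule is ill suited and ambiguous and can be replaced cheaply. It does not show that the trial's results will be wrong.

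**What to change.** 1. Remove last observation carried forward. No value should be moved from one time point to another.
2. Leave missing Feeling Scale, craving and anxiety scores missing. Analyse all observed assessments with a linear mixed model in place of the repeated-measures analysis of variance. Estimates are then valid if data are missing at random, and a participant with one gap keeps the other time points.
3. For each PANAS dimension and for self-esteem, prorate when at least half of the items are answered: (sum of answered items ÷ number answered) × number of items in the subscale, using answers from the same time point only. Otherwise set that subscale score to missing.
4. State the 50% rule per subscale, so that *questionnaire* no longer needs interpretation.
5. Report the number of missing scores by outcome, condition and time point, so that readers can judge how much rests on these rules.

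The cost is a change of model wording and slightly more analysis work; no data are lost. The Results section says that collection ended in August 2019 and places the analysis in 2020, so the change should be fixed and dated before the outcome data are analysed.
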